#### 2.9.2 Secondary analyses

In order to establish a suitable time point for administering the “Booster” of the placebo, the time course of the NRS pain score will be investigated. For each participant, the difference in the NRS pain score between the interventional visit and control visit will be calculated. We will then fit a broken stick mixed-effect model (80) assuming normal distribution of the error, including the type of visit as a fixed factor, and an identifier of the participant as a random factor. The model will account for random intercepts only. The optimal breakpoint will be selected based on the residual standard error. We will also model the time course of NRS pain with Gaussian process regression (81).

Furthermore, the AUC of areas of hyperalgesia and allodynia will be compared between the two visits in Part 1 and between the three arms in Part 2, applying the same analysis as described for the primary endpoint. The development of NRS pain score, hyperalgesia, and allodynia over time will be presented graphically.

The influence of the variables listed in “other variables of interest” (c.f. 2.6.3.) on the outcome will be analyzed by means of linear regression models with the difference between the intervention and the control visit in the area under the curve of pain, allodynia and hyperalgesia as the outcome and the arm and the score of the respective question as predictors.

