##### 2.1.1.2 Further objectives

We hypothesize that there will be a difference in the areas of hyperalgesia and allodynia when comparing subjects receiving a single OLP injection with control subjects receiving no treatment. We hypothesize that the expected difference in subjective pain ratings, hyperalgesia, and allodynia will diminish or even disappear over time as a regular end of dose phenomenon. Insight on the timing of when the effect of the placebo decreases will allow us to determine when to administer a second dose (booster) of OLP (fixed-time booster) in Part 2.

#### 2.1.2 Part 2

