##### 2.4.2.3 Timeline

Tables 1, 2 (for Part 1 and Part 2, respectively) give an overview over the timeline for each study visit.

**TABLE 1 T1:** Schedule for study procedures, part 1.

Possible OLP (intervention only)						x				
Questionnaires	x					x				x
NRS		x	x	x	x	x		x	every 5 min	x
Hyperalgesia		x		x		x		x	every 10 min	x
Allodynia		x		x		x		x	every 10 min	x
Electrical stimulation										
Time (min)	−5	0	5	10	15	20	25	30	…	200

NRS, numeric rating scale; OLP, open-label placebo.

**TABLE 2 T2:** Schedule for study procedures, part 2.

OLP / OLP Booster (Booster groups only)						x			x*	
Questionnaires	x					x			x*	x
NRS		x	x	x	x	x		x	every 5 min	x
Hyperalgesia		x		x		x		x	every 10 min	x
Allodynia		x		x		x		x	every 10 min	x
Electrical stimulation										
Time (min)	−5	0	5	10	15	20	25	30	…	**

*either on fixed time point (derived from Part 1; if data is inconclusive, at 100 min) or on-demand.

**measurement time period derived from Part 1. NRS, numeric rating scale; OLP, open-label placebo.

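### The random-intercept-only broken-stick model will overstate how precisely Part 1 shows fading and times the booster if time courses differ or successive ratings are correlated

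*Protocol article*

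**What the plan says.** Section 2.9.2 gives the purpose of the time-course analysis in its opening sentence, which begins: "In order to establish a suitable time point for administering the “Booster” of the placebo, the time course of the NRS pain score will be". The outcome is a within-person contrast: "For each participant, the difference in the NRS pain score between the interventional visit and control visit will be calculated". A broken-stick mixed model with normal errors follows, "including the type of visit as a fixed factor, and an identifier of the participant as a random factor". A difference between visits has no visit type, so I take the differences as the outcome. Two sentences then fix the model: "The model will account for random intercepts only", and "The optimal breakpoint will be selected based on the residual standard error". A Gaussian process regression of the same time course is planned as well, but it is given no part in choosing the break or in judging how firm it is.

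Two other places depend on the result. Section 2.1.1.2 hypothesises that the difference between visits "will diminish or even disappear over time as a regular end of dose phenomenon". The footnote to Table 2 in section 2.4.2.3 has the booster given "either on fixed time point (derived from Part 1; if data is inconclusive, at 100 min) or on-demand", and section 2.5.1 repeats the fallback. Neither place says how it is decided that the data are inconclusive.

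**The concern.** A model with only a participant intercept assumes that everyone follows the same course over time apart from a vertical shift, and that a person's readings scatter independently around that course. Pain ratings taken every 5 minutes from one person under continuous stimulation may well break both assumptions. The model then credits the data with more independent information about change over time than 36 people supply.

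The restriction to random intercepts is an explicit choice in the text, not a detail left open. Two judgements are at stake. One is whether Part 1 shows the analgesic difference fading, which is a stated hypothesis and bears on the duration of the effect. The other is whether Part 1 is firm enough to supply a booster time for Part 2. Both need a measure of uncertainty, and this model's own intervals are the natural one to use.

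**Working it through.** **Inputs from the protocol.** There are 36 participants (section 2.8). NRS is taken every 5 minutes after the injection (section 2.6.1), and Table 1 shows readings from 30 to 200 minutes. That makes (200 − 30)/5 + 1 = 35 differences per person, or 36 × 35 = 1,260 in all. The plan states no standard error, slope variance or error rate for this model, so there is no figure of its own to reproduce.

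**Assumptions, not in the documents.** Residual SD 0.5 or 1 NRS point. First-order serial correlation ρ of 0, 0.5 or 0.8. Between-person slope SD τ of 0, 0.5, 1 or 2 NRS points over 170 minutes.

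**Formula.** With balanced data the slope estimates at a given break are the same with or without random slopes, and only the standard error changes. Let r be the reported standard error divided by the true one. A nominal two-sided 5% test then rejects a true null with probability of about 2Φ(−1.96 r).

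**Hand check with one straight line.** Take residual SD 1, τ = 1, independent errors, and time in units of 170 minutes.
- Sum of squares of time: 25 × [35 × (35² − 1)/12]/170² = 25 × 3,570/28,900 = 3.088.
- True variance of one person's slope: 1/3.088 + 1² = 1.324.
- The model pools the slope variation into the residual: 1 + 3.088/34 = 1.091. It therefore reports 1.091/3.088 = 0.353.
- r = √(0.353/1.324) = 0.52, and 2Φ(−1.96 × 0.52) is about 31%.

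**Simulation of the post-break slope.** No fading, break fixed at 100 minutes, 600 runs per setting:

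| Setting | r | False positives |
|---|---|---|
| ρ = 0, τ = 0 | 1.0 | 4–5% |
| ρ = 0, τ = 0.5 | 0.94–0.78 | 6–13% |
| ρ = 0, τ = 1 | 0.77–0.55 | 13–27% |
| ρ = 0, τ = 2 | 0.55–0.40 | 28–44% |
| ρ = 0.5, τ = 0 | 0.61 | about 26% |
| ρ = 0.8, τ = 0 | 0.40 | 43–45% |

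The formula agrees: r = 0.77 gives 2Φ(−1.51) = 13%, and r = 0.40 gives 2Φ(−0.78), about 43%. One slope per participant, tested across participants at the same fixed break, gave 3–6% throughout.

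**Slope change at a fixed 110-minute break.** With residual SD 1 and no true change, the test rejected in 21–40% at ρ = 0.5 to 0.8, against 4–6% with independent errors. Straight-line differences between people cancel from a change in slope, so serial correlation drives this result.

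**The break itself.**
- With a true break at 120 minutes, independent errors and residual SD 1, the estimate averaged 120–121 minutes (SD about 13) for every τ from 0 to 2.
- The nominal 95% interval for that break covered it in about 64–77% of runs at ρ = 0.5 to 0.8. A separate set of runs, with a slope change of 0.75 NRS points per hour, gave 73–75% at 0.5, 62–65% at 0.8 and 92–95% with independent errors.

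**Choosing the break from the data.** With no fading, the selected break spread over the whole search range (5th to 95th percentile 50 to 180 minutes). A later slope test from the random-intercept model was positive in 13–15% even when that model was correct. Participant-level slopes tested at the selected break still rejected in about 8–15%.

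**The case against.** The strongest reply is that section 2.9.2 uses the model only to find a time point, by a criterion that involves no slope standard error. No slope test, interval or rule for declaring fading is named, and the estimated break is essentially unbiased. All of this is correct, and it limits the point to the two judgements described above. The reply does not remove the point, because an inconclusive result triggers a different booster time, and that judgement needs some view of uncertainty.

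It can also be said that the sizes rest on assumed values. They do. With no slope variation and independent errors the standard errors are right. The planned Gaussian process regression might display uncertainty, but the text gives it no role in the decision.

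A reader might infer more than the documents support:
- **That the standard errors are certainly too small.** This is conditional on slope variation or serial correlation, which the documents do not quantify.
- **That the criterion for choosing the break is wrong, or the booster time biased.** The simulations do not show this, and an autoregressive fit did not locate the break better.
- **That a false fade will be declared.** No such declaration is specified.
- **That Part 2 error rates suffer.** A poorly timed booster could weaken the contrast, but would not inflate the type I error of the randomised comparisons in section 2.9.1.
- **That random slopes alone would cure the problem.** They do not allow for choosing the break from the data.

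**Conclusion.** The point holds in conditional form. Using the random-intercept fit to locate the break is acceptable. Using its standard errors or intervals to judge fading, or to judge whether Part 1 is conclusive, is not. With residual SD 1 and serial correlation of 0.5 to 0.8, the cost is about 21–40% false positives for a slope change at a fixed break, and about 64–77% coverage of a nominal 95% interval for the break. Variation in slopes between people harms inference on the segment slopes but hardly affects the interval for the break. With independent errors and no or small slope variation, both measures are near nominal. The direction of the error is secure when either condition holds. Its size depends on correlation and slope variance that the documents do not give. The matter deserves correcting before Part 1 is analysed, but it does not touch the primary analyses.

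**What to change.** Keep the random-intercept fit and the residual-error criterion to locate the break. After those sentences in section 2.9.2, add wording such as:

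> Uncertainty for the segment slopes and the breakpoint will come from a bootstrap that resamples whole participants and repeats the breakpoint search in every resample. Standard errors from the random-intercept model will not be used for inference. The bootstrap intervals will be used to judge whether the effect diminishes and whether the Part 1 data are inconclusive.

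Resampling whole participants carries both the slope differences and the serial correlation, with no need to model either. Repeating the search allows for selection of the break, which a slope test at the selected break ignores. In a check under the same assumptions with a true break at 120 minutes, this interval covered the break at or slightly above its nominal rate. How wide an interval counts as inconclusive is for the investigators to fix in advance.

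The cost is a few sentences and a little more computing, with no new data. The downside is wider intervals, which may make it more likely that Part 1 is judged inconclusive.

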#### 2.6.3 Other variables of interest

Other variables of interest are:

•Placebo attitudes & beliefs•Treatment expectations•Credibility of intervention•Safety outcomes

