##### 2.6.3.3 Credibility of intervention

If receiving an OLP injection, participants will be asked about the credibility of the OLP intervention at the end of the study visit (for details cf. Supplementary material).

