#### 2.6.4 Safety outcomes

Due to the “inert” nature of placebos, no specific adverse events are expected. However, safety endpoints including the patient’s well-being, pain, skin irritation/infection, and allergic reactions/hypersensitivity will be noted. Thereby, we will assess adverse events of the pain model and/or the infusion of fluids through the venous access.

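### Credibility is rated at the end of the OLP visit, so the planned Part 1 regression cannot show its influence on pain during that visit

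*Protocol article*

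**What the plan says.** Section 2.9.2 states: "The influence of the variables listed in “other variables of interest” (c.f. 2.6.3.) on the outcome will be analyzed". The method is linear regression, "with the difference between the intervention and the control visit in the area under the curve of pain, allodynia and hyperalgesia as the outcome", and with "the arm and the score of the respective question as predictors". No listed variable is excepted.

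The list in section 2.6.3 has four entries: placebo attitudes and beliefs, treatment expectations, credibility, and safety outcomes. Their timing is given in the sections that follow:

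- Attitudes and beliefs (2.6.3.1) are taken before the pain model is set up, and in Part 1 at the first visit only.
- Expectations (2.6.3.2) are taken before the intervention. In Part 2 they are also taken before the booster.
- Credibility (2.6.3.3): "If receiving an OLP injection, participants will be asked about the credibility of the OLP intervention at the end of the study visit".
- Safety (2.6.4): "safety endpoints including the patient’s well-being, pain, skin irritation/infection, and allergic reactions/hypersensitivity will be noted".

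**The concern.** The regressions are meant to say which participant characteristics shape the response to OLP. To be read that way, a predictor must be fixed before the response occurs. Attitudes, beliefs and pre-injection expectations meet this condition. Credibility does not, because the participant gives the rating after about three hours of feeling relief or none. A person who felt less pain may find the injection more credible for that reason alone, and the same coefficient would appear whether credibility drove the relief or followed from it.

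At stake is a statement about mechanism. The treatment rationale in section 2.5.1.1 presents expectation as an important route to placebo analgesia, so a result naming credibility as an influence would be read with interest, and the design could not support it.

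**Working it through.** The plan gives no figure on this point, so the check is first one of order in time, then an illustration.

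**Order of events in the OLP visit of Part 1**

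1. Before the pain model is set up: attitudes and beliefs, if this is the first visit (2.6.3.1).
2. Minute 0 to 15: stimulation and adjustment of the current (2.4.2.2).
3. Minute 20: expectations asked before the intervention, then the OLP injection (2.6.3.2; 2.5.1; Table 1).
4. Minute 20 to 200: pain ratings that form the AUPC, 200 − 20 = 180 min, which is the 3 h of section 2.6.1.
5. End of visit: credibility (2.6.3.3; last questionnaire mark in Table 1, at 200 min).

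Items 1 and 3 precede the outcome window and item 5 closes it. For participants who receive OLP at the second visit, both AUCs in the difference are complete when credibility is rated. For those who receive OLP first, the control visit is still to come, but the OLP half of the difference is complete.

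**Illustration of what the model would show without any influence**

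Inputs from section 2.8: N = 36, SD of the AUPC difference 67, mean difference 45 (entered as −45, a reduction). Assumptions: 18 participants per sequence, credibility with no causal effect on pain, and a correlation r between relief and the later rating. The documents give no value for r, so a range is shown.

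Approximate power of a 5% correlation test by Fisher's z is Φ(atanh(r) × √(36 − 3) − 1.96), with √33 = 5.745:

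- r = 0.3: 0.3095 × 5.745 − 1.96 = −0.18, giving 42.8%
- r = 0.4: 0.4236 × 5.745 − 1.96 = 0.47, giving 68.2%
- r = 0.5: 0.5493 × 5.745 − 1.96 = 1.20, giving 88.4%

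A simulation of the planned model (visit difference on sequence arm and score, 4,000 runs) agrees:

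| r | p < 0.05 for the score | mean slope per SD of score |
|---|---|---|
| 0 | 4.8% | −0.05 |
| 0.2 | 19.7% | −13.0 |
| 0.3 | 42.3% | −19.9 |
| 0.5 | 88.4% | −33.5 |

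The slopes are close to −r × 67 (for r = 0.3, −20.1). A rating that only mirrors the outcome can thus produce a slope of a size that matters beside the assumed effect of 45.

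**Safety outcomes**

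Section 2.6.4 names pain among the safety endpoints. Taken literally, the cross-reference to 2.6.3 would place pain among the predictors of pain AUC. Section 2.6.4 gives safety no question and no score, so the predictor definition in 2.9.2 does not fit it.

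**The case against.** Several points on the other side have force.

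- **Nothing shown says that relief raises credibility ratings.** The credibility items are in supplementary material that is not at hand, and they may ask about the rationale rather than about benefit. This stands: reverse causation is a possibility that the model cannot exclude, not an established fact.
- **The percentages are close to circular.** They are the power to detect an association assumed to be real, and section 2.9.2 sets no significance threshold for these models. This also stands. They show only that a real association would often be detected and could then be misread as influence.
- **No confirmatory claim is attached.** The objectives contain no hypothesis on these variables, and section 3 describes the study as looking for hypotheses to test later. That limits the weight of the point. The explicit exploratory statement, however, covers the sensitivity analyses in 2.9.3 and not these regressions.

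Two stronger readings are tempting, and the text does not support them. A reader might infer that the plan specifies an impossible analysis for Part 2, where each participant has one visit. But an outcome defined as a difference between an intervention and a control visit makes this a Part 1 model by its own terms. That no Part 2 model is described is detail a condensed article may leave to the full protocol or analysis plan. A reader might also infer that the plan intends to regress AUC on adverse events. The predictor is the score of a question, which suggests that safety was swept in by a loose cross-reference.

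**Conclusion.** The point holds for credibility in Part 1. Its coefficient can be computed and reported as an association, but it cannot be read as influence on the AUC difference, because the rating follows the pain ratings of the OLP visit. This conclusion rests on timing alone and needs no assumed correlation. How far the coefficient would be distorted is unknown; the 43% to 88% range is illustrative and depends wholly on the assumed r of 0.3 to 0.5. The safety entry is a cross-reference to correct, and the confinement to Part 1 is a matter to state. The analysis is secondary: the primary tests, the sample sizes and the choice of booster time are unaffected.

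**What to change.** In section 2.9.2, or in the analysis plan:

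1. Limit the influence models to scores obtained before the OLP injection: attitudes, beliefs and pre-injection expectations.
2. Report credibility as a post-treatment association, or as an outcome in its own right.
3. Correct the cross-reference to 2.6.3 so that safety outcomes are described separately and not entered as predictors.
4. State that the model with the visit difference as outcome applies to Part 1.
5. If these variables are also modelled in Part 2, use the participant's own AUC as outcome with the randomised arm in the model. Count only expectations asked before the first injection as pre-treatment, since those asked before the booster fall within the pain course.

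The cost is a few sentences, settled before the analysis. No new data are needed and no measurement changes.

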#### 2.9.3 Sensitivity analyses

In order to further examine the effect of OLP application on subjective pain ratings, the following sensitivity analyses will be conducted:

1.In order to be able to directly compare the results with previous studies (55), we will repeat the primary analysis for a restricted AUPC using only the first 90 min of measurement.2.We will explore the relationship between the outcome and the time between the two visits by fitting a linear regression model with the difference in the AUPC as the outcome and the arm, the time between the visits and the interaction term arm × time between visits as predictors.3.We will examine the relationship between the difference in the AUPC and several demographic covariates namely (i) age (ii) sex, and (iii) level of education. To this end, we will fit linear regression models with the difference in the AUPC as the outcome and the arm, the covariate and the interaction term arm × covariate as predictors.

These sensitivity analyses are exploratory and not confirmatory, hence no hypotheses are tested and *p*-values will be interpreted as continuous measures that inform the generation of new hypotheses worthy of further investigation.

#### 2.9.4 Interim analyses

No interim analysis is planned.

### 2.10 Monitoring

The study will be monitored for quality and regulatory adherence by an independent monitor of the University Hospital of Basel. The monitor will verify the qualifications of the investigators and study team members and control for sound and appropriate documentation. In addition, monitoring visits will serve to ensure that:

•The study is being conducted according to the study protocol and within the specified time frame.•Data are collected accurately and are completely documented in REDCap, and the source documents.•The interventional medication (placebo injections) are being correctly prepared, dispensed and accounted for.•Side effects are being correctly defined, assessed, and documented.

## 3 Discussion

Placebo effects have already been observed for a long time. Since Beecher’s often-quoted 1955 study (82), several publications have reported on placebos and placebo effects. Hrobjartsson and Gotzsche (13) provide a nice overview. Significant effects on various conditions have been found, especially patient-reported outcomes, such as pain (13, 16). However, ethical concerns about the deceptive use of placebos have grown (18–20). Therefore, OLPs have been proposed (21) as a means of using placebos in an ethical manner. There is a rising body of knowledge concerning OLPs, and they have been proven to be effective in various clinical conditions including chronic pain. Charlesworth et al. (56) and von Wernsdorff et al. (57) provide an overview of these effects.

Although a well-known challenge, pain management remains difficult in many situations. Therapy options are limited, and positive effects are often diminished by contraindications, side effects, and adverse events (e.g., 2–8). This illustrates the need for new broadly applicable treatments, preferably with few or no side effects, which could augment existing multimodal analgesic concepts (7). OLPs potentially fit this description given the near absence of contraindications and few if any side effects, which are likely avoidable and usually present as nocebo effects (11, 17). Already, a small amount of evidence supports the use of OLPs in acute pain (25–29, 47, 49, 52, 53). However, for clinical implementation, the efficacy of these interventions need to be characterized to a greater extent. This study contributes to this by measuring the duration of OLP analgesia in acute pain. To our knowledge, this is the first study investigating whether repeated OLP doses are more beneficial than a single-dose and when repeated dosing should occur.

A strength of this study is the cross-over design of Part 1, in which participants serve as their own control, thereby enabling comparison between the interventional and control group. Part 2 does not have a cross-over design. Rather, participants are randomized into three different groups, establishing the classic form of randomized controlled trial. In addition, all procedures will be highly standardized, as the same investigators and respective study staff will be interacting with all participants included in each study part. Further strengths include the use of a well-established pain model (61) and the long 200-min measurement period. Finally, in this experimental setting, the assessor will perform measurements every 5 min, which should result in no missing data, contrary to what would be expected for experiments utilizing self-reported questionnaires.

This study also has a few limitations. As this is an experimental study with highly standardized procedures, results will have to be transferred to clinical application with caution. The placebo effect could be altered in clinical populations with possible interfering variables such as comorbidities [particularly if the cognition is impaired (83)], concomitant medication, (negative) emotions (84) or deviant procedures [e.g., no sufficient OLP rationale (26)]. In summary, with this study, we strive to find hypotheses concerning OLPs, which can later be translated to and tested in clinical populations (32).

Three further factors compromise generalizability. First, the population will be recruited through an advertisement on the homepage of the local university, which may lower the diversity of the study population. Second, some bias cannot be ruled out. Due to the nature of OLPs, blinding of participants is not possible. In addition, due to organizational reasons, even the assessor will not be blinded to the intervention in Part 2. Furthermore, it could also be argued, that not providing an interventional rationale to the control group in Part 1 could result in a difference in patient-provider relationship between interventional and control group. Third, for Part 1, we assume that there are no carry-over effects (i.e., we assume that the treatment sequence will not modify the treatment effect). Specifically, while we account for period effects (e.g., in the form of learning to better deal with pain from the first to the second treatment period), we assume that this will not depend on whether the participant received the placebo or the control intervention during the first visit.

In addition, the measurement period could also be seen as a limitation: Although with 200 min it is quite long, and – to our knowledge – longer than the observation time of previous comparable studies, it could still be insufficiently long to fully observe OLP analgesia for acute pain.

In conclusion, although the study faces a few limitations, we are convinced that it has been designed in a way that will extend the knowledge about the use of OLPs in the treatment of acute pain. In particular, the duration of OLP analgesia and possible “Booster” effects will need to be evaluated before implementation to clinical practice is possible. Therefore, this study will add another step towards clinical implementation of a new, broadly applicable treatment for acute pain with few to no contraindications or side effects.

